# GEICO1601-ROLANDO: a multicentric single arm Phase II clinical trial to evaluate the combination of olaparib and pegylated liposomal doxorubicin for platinum-resistant ovarian cancer

**DOI:** 10.4155/fsoa-2018-0107

**Published:** 2019-01-10

**Keywords:** maintenance, olaparib, ovarian cancer, pegylated liposomal doxorubicin, platinum-resistant

## Abstract

Response to polyadenosine diphosphate ribose polymerase (*PARP*) inhibitors in platinum-resistant ovarian cancer and in the absence of *BRCA* mutations is very low. Combining PARP inhibitors with other agents might overcome this lack of activity. Here we describe the rationale and design of GEICO1601-ROLANDO (resistant ovarian cancer treated with olaparib and pegylated liposomal doxorubin; NCT03161132). ROLANDO is a Phase II single-arm multicenter trial in which patients are treated with a combination of olaparib and pegylated liposomal doxorubicin (PLD) in platinum-resistant epithelial ovarian, primary peritoneal, or Fallopian tube cancer regardless of the *BRCA* mutation status. The primary end point is progression-free survival at 6 months. Other secondary end points are response rate, disease control rate, quality of life and overall survival.

Ovarian cancer is a leading cause of death, being the fourth most frequent cause of mortality in women in developed countries [1].

Family history and the presence of mutations in genes such as *BRCA1* and *BRCA2* significantly increase the risk of development of ovarian cancer; other factors such as hormonal or reproductive factors can either increase or decrease the likelihood of this disease [2].

The overall median survival for ovarian cancer is about 40–50% at 10 years from diagnosis. However, this falls significantly to 21% and <6% when the disease is diagnosed at Stages III and IV, respectively. Approximately 90% of ovarian cancers are epithelial in origin, of which 60–70% are high-grade serous ovarian cancer [3].

Epithelial ovarian cancer is highly chemosensitive and the current standard of care for newly diagnosed cases involves debulking surgery and adjuvant platinum- and taxane-based combination chemotherapy. Although most patients achieve a remission with front-line therapy, unfortunately, up to 80% of patients will relapse [4]. Disease recurring >6 months from the last platinum-based chemotherapy is considered as platinum-sensitive relapse while recurrences within the first 6 months are classified as platinum resistant. Platinum sensitive is more likely to respond to platinum-based chemotherapy; however, the development of platinum resistance is an inevitable event [5].

The development of *PARP* inhibitors for the treatment of tumors deficient in *BRCA1* or *BRCA2* is driven by the concept of synthetic lethality, a phenomenon in which the individual deletion of two independent genes does not cause cell death, but the combined deletion is cytotoxic.

Olaparib (AZD2281) is an oral *PARP*-1 and -2 inhibitor largely tested among ovarian cancer patients. In the Phase I clinical trial patients with different solid tumors refractory to standard treatment were included. Partial response and clinical benefit were observed in those patients harboring BRCA mutation diagnosed with breast, ovarian and prostate cancer [6].

The expansion cohort of this Phase I trial finally included 50 *BRCA* mutation carriers with platinum-refractory (26%), platinum-resistant (48%) and platinum-sensitive relapse (26%) [7]. Olaparib, at different dose levels, achieved a 28% of response rates by response evaluation criteria in solid tumors (RECIST; 95% CI: 16.2–42.5%), 46.2% in platinum-sensitive and 33.5% in platinum-resistant recurrences, with no responses in the platinum-refractory group. Clinical benefit was also meaningful with 46% in the whole series, which was particularly relevant in the platinum-sensitive group (69.2%), but also interesting in the platinum-resistant (45.8%) and -refractory (23.1%) groups.

A later Phase II trial finally confirmed the activity of olaparib in monotherapy in a heavily pretreated *gBRCAmut* ovarian cancer population. In this international study, patients irrespective of interval of platinum were treated after a median of three previous lines in two different cohorts with olaparib 400 mg two-times a day (b.i.d.) and 100 mg b.i.d. Overall response rate (ORR) was 30% in the cohort treated with 400 mg and 13% in the cohort with olaparib 100 mg. The most frequent adverse events were nausea, fatigue and anemia, which were slightly superior in the cohort of 400 mg b.i.d. [8].

In 2012, a multicentre Phase II study by Kaufman *et al*. enrolled individuals with a germline *BRCA1*/2 mutation and recurrent cancer. Eligibility included ovarian cancer resistant to prior platinum; breast cancer with more than or equal to three chemotherapy regimens for metastatic disease; pancreatic cancer with prior gemcitabine treatment; or prostate cancer with progression on hormonal and one systemic therapy. Olaparib was administered as a single agent at 400 mg b.i.d. The primary efficacy end point was tumor response rate. A total of 298 patients received treatment. The tumor response rate was 31.1% in the ovarian cancer cohort (all platinum resistant; Tables 1 & 2) [9].

**Table 1. T1:** **Trials with olaparib in platinum-resistant ovarian cancer harboring BRCA mutations.**

**Study (year) [Ref.]**	**Design**	**n**	**Setting**	**Response rate/clinical benefit rate**	**Platinum-resistant relapse**
Fong *et al*. (2010) [7]	Phase I trial. Expansion cohort of olaparib 400 mg b.i.d. End point: response	50	*BRCA* mutated (41 *BRCA1*, 8 *BRCA2* mutation confirmed, one strong family history)	ORR (CR + PR) 28% (16.2–42.5); CBR 46% (31.8–60.7%)	n = 24 platinum resistant, ORR 33.5% (15.6–55.3), CBR 45.8% (25.6–67.2); n = 13 platinum refractory, ORR 0% (0–24.7), CBR 23.1% (5–53.8)

Kaufman *et al*. (2015) [9]	Phase II (including ovarian, breast, pancreas, prostate and other cancers). End point: response	218 Ovarian cancer 193	*BRCA*-mutated ovarian cancer: 148 *BRCA1* 44 *BRCA2* 1 *BRCA1* and *BRCA2*	ORR 26.2% (21.3–31.6)	n = 193, ORR 31.1% (24.6–38.1)

b.i.d.: Two-times a day; CBR: Clinical benefit rate; CR: Complete response; ORR: Overall response rate; PR: Partial response.

**Table 2. T2:** **Trials with olaparib in platinum-resistant ovarian cancer irrespectively of BRCA mutation status.**

**Study (year) [Ref.]**	**Design**	**n**	**Setting**	**Response rate in overall population**	**Response rate in *BRCA*-mutated population**	**Response rate in *BRCA* wt population**
Gelmon *et al*. (2011) [10]	Phase II single arm (olaparib 400 b.i.d.). End point: response	91 (65 ovarian cancer)→17 *BRCA* mut and 47 *BRCA* no mut	Recurrent ovarian cancer. Median 3 previous lines (1–10)	OR 29%	60% (3/5 platinum sensitive); 33% (4/12 platinum resistant)	50% (10/20 platinum sensitive); 4% (1/26 platinum resistant)

Based on the study by Kaufman *et al*., olaparib was approved by the US FDA for refractory, advanced ovarian cancer associated with germline breast cancer susceptibility gene (*BRCA*) mutations in 2014. In August 2017, olaparib was additionally approved by the FDA as a maintenance therapy for women with recurrent epithelial ovarian, fallopian tube or primary peritoneal cancer who have achieved complete or partial response to platinum-based chemotherapy, irrespective of their *BRCA* status.

However, EMA approval of olaparib has been limited to platinum-sensitive relapse.

Olaparib was compared with pegylated liposomal doxorubicin (PLD) in a multicenter randomized Phase II trial. Patients with BRCA1 or BRCA2 germline mutations recurring within 12 months of prior platinum therapy were randomized to receive olaparib 200 mg b.i.d. versus olaparib 400 mg b.i.d. versus PLD 50 mg/m^2^ intravenously every 28 days [11]. 97 patients were included, of whom 42.4–56.4% were platinum resistant. Of note, the proportion of platinum-resistant relapses was inferior in the PLD arm (42.4%). Progression-free survival (PFS) was 6.5 months (95% CI: 5.5–10.1 months), 8.8 months (95% CI: 5.4–9.2 months) and 7.1 months (95% CI: 3.7–10.7 months) for olaparib 200 mg, olaparib 400 mg and PLD, respectively, with an unexpectedly high PFS for the PLD arm. There were no statistically significant differences between combined arms of single agent olaparib versus PLD (HR: 0.88; 95% CI: 0.51–1.56; p = 0.66). RECIST-assessed response rates were 25, 31 and 18%, respectively, with no statistically significant differences. This study showed a similar activity and a trend toward improvement with olaparib versus PLD in patients with relapsed ovarian cancer and *BRCA1* or *BRCA2* mutations.

Although olaparib has been tested in combination to chemotherapy with carboplatin and paclitaxel in a randomized Phase II trial [12], the only previous experience of a combination of PLD and concurrent olaparib comes from a Phase I trial [13].

## The ROLANDO trial

Here we describe the rationale and design of ROLANDO, a single-arm Phase II trial, designed to evaluate the efficacy and safety of the combination of olaparib plus PLD in platinum-resistant epithelial ovarian cancer.

### Background & rationale

The combination of olaparib and liposomal doxorubicin in ovarian cancer has been tested previously in a Phase I trial [13]. 44 patients with ovarian (n = 28), breast (n = 13) and other solid tumors (n = 3) were treated with olaparib continuously (days 1–28) or intermittently (days 1–7) plus PLD (40 mg/m^2^ day 1). Seven olaparib cohorts were explored (50–400 mg b.i.d.) to determine the recommended dose. Olaparib 400 mg b.i.d. plus PLD was well tolerated and no dose lethal toxicity was detected. Grade 3 adverse events (AE) were reported in 27 patients (61%), and serious AE occurred in 12 patients (27%). Most frequent Grade 3 AE were stomatitis, nausea and asthenia, which happened mainly in the cohort of olaparib 400 mg b.i.d. continuously.

No major interactions were observed between PLD and olaparib. The ORR was 33% (14 out of 42 patients, three complete responses). A total of 13 responders had ovarian cancer (response rate 46.4% in ovarian cancer), of whom ten were platinum sensitive.

Recently, a preclinical study demonstrated a synergism of the combination of olaparib with doxorubicin in 2D and spheroid models of ovarian cancer [14]. This study showed that DNA damage was increased at a molar concentration of doxorubicin: olaparib of 50:1 in both *BRCA* mutant and *BR CA* wild type cell lines UWB1-289. The combination of PLD and olaparib resulted in a significantly increased number of double-strand breaks assessed by γ *H2AX* assay compared with olaparib single agent (approximately 10- and 13-fold increases for UWB1.289 and UWB1.289 +*BRCA*, respectively) and to doxorubicin single agent (approximately 50 and 65% increases, respectively).

### Design

#### Study design

GEICO 1601-ROLANDO (NCT03161132) is a single-arm prospective trial to assess the efficacy and safety of the combination of olaparib and PLD in the platinum-resistant setting.

#### Primary & secondary objectives

Primary efficacy end point is 6 months PFS rate (PFS6m) of the combination of olaparib 300 mg b.i.d. in tablet formulation + PLD 40 mg/m^2^ intravenously every 28 days followed by olaparib 300 mg b.i.d. tablet formulation in platinum-resistant relapsed ovarian cancer patients.

Secondary end points are safety and objective response rate (ORR), defined as the sum of complete and partial responses by RECIST 1.1, disease-control rate (complete response, partial response or stable disease), CA-125 response, PFS, postprogression survival, overall survival, quality of life and growth-modulation index.

#### Key eligibility criteria

Key eligibility criteria are shown in Table 3.

**Table 3. T3:** **Key inclusion and exclusion criteria.**

**Key inclusion criteria**	**Key exclusion criteria**
Platinum-resistant recurrent high-grade serous or endometrioid ovarian cancer, primary peritoneal or fallopian tube cancer (>28 days and <6 months since previous platinum)	Platinum-refractory ovarian cancer (relapse during or <28 days since last platinum-containing chemotherapy)

≤3 prior chemotherapy regimens	Previous therapy with *PARP* inhibitor

Any *BRCA* status: – *BRCA* wt or unknown: at least one previous platinum-sensitive relapse – *BRCA* mut: primary platinum resistance is allowed	Previous therapy with PLD except if > 6 months since last PLD and given as a part of a platinum-sensitive relapse

ECOG ≤2	LVEF less than threshold of normality

Measurable disease according to RECIST 1.1	

Adequate renal, liver and bone marrow function (Hb ≥10 g/dl)	

ECOG: Eastern Cooperative Oncology Group; Hb: Hemoglobin; LVEF: Left ventricular ejection fraction; PLD: Pegylated liposomal doxorubicin; RECIST: Response evaluation criteria in solid tumors.

#### Planned sample size

The sample size was determined based on exact single-stage Phase II design. We assumed that a new combination with 6-month PFS of 15% or less would be considered of little clinical significance and that an agent with PFS 40% or higher would be of interest for further investigation. With 90% power and at a two-sided 0.05 significance level, 27 evaluable patients should be included in the study, requiring at least ten patients surviving after 6 months to reject the null hypothesis.

In order to obtain the required evaluable number of patients we expect to recruit 32 patients (20% dropouts).

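### The rule of at least 10 of 27 has 69% power and 0.4% one-sided type I error, not 90% power at two-sided 0.05

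*Protocol article*

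**What the plan says.** The design is set out in one paragraph of the protocol article, Planned sample size.

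- Method: "The sample size was determined based on exact single-stage Phase II design".
- Null rate: "a new combination with 6-month PFS of 15% or less would be considered of little clinical significance".
- Target rate: "an agent with PFS 40% or higher would be of interest for further investigation".
- Error rates: "With 90% power and at a two-sided 0.05 significance level".
- Size and decision rule: "27 evaluable patients should be included in the study, requiring at least ten patients surviving after 6 months to reject the null hypothesis".
- Recruitment: "we expect to recruit 32 patients (20% dropouts".

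The executive summary repeats the 15%, the 40% and the 32 patients, but not the cut-off. The Statistical analysis section says that the primary end point will be estimated by Kaplan–Meier, primarily in all patients who received at least one dose. It gives no other criterion for rejecting the null hypothesis.

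**The concern.** In an exact single-stage design, the sample size, the cut-off and the two rates fix the type I error and the power completely. Ten of 27 is 37%, only just below the 40% target. A trial whose true rate is 40% expects 27 × 0.40 = 10.8 successes, so a cut-off of ten lies close to the middle of that distribution, and 90% power is implausible on sight.

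This is the only rule in the document for declaring the combination worth pursuing. If it is too strict for its sample size, the type I error is protected and the loss falls on power: an active combination is more likely to be dropped than the plan says.

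The rule also counts patients surviving at 6 months, while the primary end point is progression-free survival at 6 months. Read literally, a patient alive after progression would count as a success.

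**Working it through.** **Inputs**, all from Planned sample size: p0 = 0.15, p1 = 0.40, n = 27, cut-off r = 10, power 90%, two-sided 0.05. I read two-sided 0.05 as 0.025 in the upper tail, the only tail in which the combination can succeed.

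**Formula.** With X the number progression-free at 6 months and X ~ Bin(n, p):

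P(X ≥ r | p) = Σ (from k = r to n) C(n, k) p^k (1 − p)^(n − k)

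Type I error is this sum at p = 0.15 and power is the sum at p = 0.40.

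**Step 1: the stated rule.** For n = 27 and r = 10:

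- P(X ≥ 10 | 0.15) = 0.0042
- P(X ≥ 10 | 0.40) = 0.6913, so the false-negative risk at 40% is 1 − 0.6913 = 0.3087

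The stated 90% is not reproduced. The shortfall is 90 − 69.1 = 20.9 percentage points.

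**Step 2: other cut-offs at n = 27.**

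| Cut-off | Type I error (upper tail) | Power at 40% | Meets 0.025 upper tail | Meets 90% power |
|---|---|---|---|---|
| ≥ 8 | 0.0398 | 0.905 | no | yes |
| ≥ 9 | 0.0138 | 0.816 | yes | no |
| ≥ 10 | 0.0042 | 0.691 | yes | no |
| ≥ 11 | 0.0011 | 0.542 | yes | no |

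No row meets both criteria.

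**Step 3: smallest exact design with at least 90% power.** For each n, take the lowest cut-off that respects the upper-tail level, and stop at the first n whose power reaches 90%.

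| Upper-tail level | Smallest n | Cut-off | Type I error | Power |
|---|---|---|---|---|
| 0.05 (one-sided 0.05) | 27 | 8 | 0.0398 | 0.905 |
| 0.025 (two-sided 0.05) | 33 | 10 | 0.0195 | 0.908 |

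The 27 in the text is the sample size of the first design, and the ten is the cut-off of the second. It looks as if two designs were joined, although the document does not prove it.

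**Step 4: other methods.** Normal approximation, two-sided 0.05, 90% power: n = 28.2, or 32.1 with continuity correction. Arcsine: 31.9. None gives 27, and none changes the exact power of ten of 27.

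**Step 5: results just below the cut-off.**

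- 9 of 27 (33%): upper-tail p = 0.0138, exact 95% confidence interval 16.5% to 54.0%. This excludes 15%, so it is significant at the stated two-sided level, yet the rule calls it negative.
- 8 of 27 (30%): upper-tail p = 0.0398, exact 95% confidence interval 13.8% to 50.2%. This is significant at one-sided 0.05 but not at two-sided 0.05.

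**The case against.** The arithmetic is not in dispute. The case on the other side concerns what went wrong and how much it matters.

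- **The cut-off may not be the slip.** The rates, the power, two-sided 0.05 and the cut-off of ten all agree with n = 33, so 27 could be the single wrong number. This stands: the document does not show which element is in error. As printed, though, ten is the wrong cut-off for 27 patients at the stated power.
- **Ten might be meant for all recruited patients.** The primary set is everyone dosed, and 32 are to be recruited. Ten of 32 gives a type I error of 0.0156 and power of 0.884. That is close to 90% but still below it, and the sentence ties ten to the 27 evaluable patients. It does show that the 31% false-negative risk holds for exactly 27 counted patients.
- **Kaplan–Meier estimation.** A Kaplan–Meier estimate with censoring does not map onto a count. True, but this leaves the operating characteristics of the stated count rule unchanged.
- **Two-sided 0.05 can be defined otherwise.** With the minimum-likelihood two-sided p-value, 30 patients with a cut-off of nine reach 90.6% power. At 27 patients that test also needs nine (p = 0.052 for eight), so power is again 81.6%.
- **Eight of 27 is not wrongly excluded at the stated level.** Correct. Only nine of 27 is excluded against the plan's own alpha.
- **The type I error is conservative.** Correct. The damage is to power alone.
- **Surviving is loose wording.** Probably so, since the same paragraph defines the rates as 6-month progression-free survival. It still sits inside the decision rule and is easily corrected.

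**Conclusion.** The concern holds. The rule as written has 69.1% power at the 40% target against the stated 90%, a false-negative risk of 30.9% against 10%, and a one-sided type I error of 0.42%. No cut-off at 27 patients delivers the stated combination of 90% power and two-sided 0.05.

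This rests on 27 patients, each with a known 6-month status, and on two-sided 0.05 meaning 0.025 in the upper tail. The 69.1% itself does not depend on the second assumption. Which of the sample size, cut-off or sidedness was misprinted cannot be settled from the article. Because this is the trial's only decision rule, it must be corrected.

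**What to change.** Return to the original sample size calculation and restate sample size, cut-off, sidedness and power together, before any 6-month outcome is reviewed. Four consistent versions are available:

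| Version | Type I error (upper tail) | Power | Cost |
|---|---|---|---|
| ≥ 9 of 27, two-sided 0.05 | 0.0138 | 82% | lower stated power |
| ≥ 8 of 27, one-sided 0.05 | 0.0398 | 90.5% | looser alpha than stated |
| ≥ 10 of 27, unchanged | 0.0042 | 69% | the low power is disclosed |
| ≥ 10 of 33, two-sided 0.05 | 0.0195 | 90.8% | six more evaluable patients |

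The first three need only a wording amendment to the protocol and the analysis plan, with no extra patients. The first keeps the stated alpha. The second keeps the stated power, but lowers the bar in a single-arm trial and should be adopted only if the original calculation was one-sided. The fourth keeps every stated parameter except the sample size. With 20% dropout it means recruiting 33 / 0.80 = 41.25, so 42 patients against the 32 planned.

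The article reports 16 patients already recruited. If 6-month outcomes have been seen, leave the cut-off at ten and correct only the stated power and alpha, because a cut-off lowered after the results are known would not be credible.

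In every version, define success as alive and progression-free at 6 months. State which patients form the denominator and how a patient censored before 6 months is counted, so that the count rule and the Kaplan–Meier estimate cannot lead to different conclusions.

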#### Efficacy evaluation

For efficacy assesment subsequent CT scan tumor evaluation according to RECIST 1.1 criteria will be performed systematically every 8 weeks. Tumor assessment will also be done at planned intervals. Visits will include systematically only physical examination and CA-125 analysis.

Patients must have been treated with at least two cycles in order to be considered evaluable. After six cycles of PLD plus olaparib, the patient will be assessed for response to treatment, and only those patients achieving response or stable disease will go on to the maintenance phase.

Disease follow-up will be done according to RECIST criteria V1.1, computed tomography scans, which should be performed at screening and every 8 weeks during the first 12 months and every 12 weeks after 12 months from start of treatment, both until disease progression.

Also, CA-125 levels will be followed, CA-125 determinations should be performed at screening and every 8 weeks during the first 12 months and every 12 weeks after 12 months from start of treatment, both until disease progression. Rising of CA-125 will not be considered progression until availability of confirmatory computed tomography scan.

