## Conclusion

The GEICO 1601-ROLANDO trial is a study that aims to respond to the question of whether the combination of PLD and olaparib has a role in the platinum-resistant setting irrespective of *BRCA* mutation status.

Executive summary
*PARP* inhibitors (PARPi) have shown important activity in platinum-sensitive relapse and BRCA-mutated ovarian cancer. However, activity of PARPi is modest in platinum-resistant relapse and *BRCA*-unknown or not mutated patients.The GEICO1601-ROLANDO trial is a single-arm Phase II trial designed to evaluate the efficacy and safety of the combination of olaparib and pegylated liposomal doxorubicin (PLD) in platinum-resistant ovarian cancer irrespectively of BRCA mutation status.Primary end point is progression-free survival (PFS) at 6 months.Secondary end points are safety, overall response rate, disease-control rate, CA-125 response, PFS and overall survival.Among the key inclusion criteria are high-grade serous or endometrioid ovarian carcinoma, platinum resistance relapse defined as >28 days and <6 months since last platinum-containing schedule, no more than three previous lines, if *BRCA* status is unknown or nonmutated at least one previous platinum-sensitive relapse is required, if *BRCA* is mutated primary platinum resistance is allowed, an Eastern Cooperative Oncology Group less than or equal to two, measurable disease and appropriate bone marrow and renal and hepatic function. Previous PLD is allowed if given during a platinum-sensitive relapse and > 6 months. Previous PARPi is excluded.PLD will be administered at 40 mg/m^2^ every 28 days in combination with olaparib tablets 300 mg/12 h continuously for six cycles followed by maintenance with olaparib. The planned sample size was calculated assuming that PFS6m 15% or less will be clinically futile and that PFS6m 40% or higher is clinically relevant. Sample size needed with 20% dropouts is 32 patients.To date 16 patients have been recruited; results are expected for the end of 2019.

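### Recruiting 32 patients with a 20% loss gives 25 to 26 evaluable patients, not the 27 required; 32 tolerates a loss of at most 5 (15.6%)

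*Protocol article*

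**What the plan says.** In the protocol article, Planned sample size, the design is an exact single-stage one with a 6-month PFS rate of 15% as uninteresting and 40% as worth pursuing. It concludes that "27 evaluable patients should be included in the study", with rejection of the null hypothesis "requiring at least ten patients surviving after 6 months to reject the null hypothesis". The next paragraph gives the recruitment target: "In order to obtain the required evaluable number of patients we expect to recruit 32 patients (20% dropouts"). The executive summary in the Conclusion repeats the pairing: "Sample size needed with 20% dropouts is 32 patients".

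Efficacy evaluation says who counts: "Patients must have been treated with at least two cycles in order to be considered evaluable". Statistical analysis bases the efficacy analyses first on an intention-to-treat set, defined as everyone given at least one dose, and second on a per-protocol set that requires at least two cycles.

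**The concern.** A dropout percentage normally refers to the patients recruited. If a share d of N recruits is lost, N(1 - d) remain, so the target must be n/(1 - d). The article's target is smaller than that formula gives, so on the plan's own assumption the trial should expect to fall short of the evaluable number on which its sample size rests.

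Two things are at stake. The first is accuracy: a sample-size statement made twice cannot be true as written. The second is power: success is fixed as a count (ten), not a proportion, so each evaluable patient lost lowers the chance of reaching it under any rule applied to evaluable patients.

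**Working it through.** **Inputs.** From Planned sample size: 27 evaluable patients required, 32 to be recruited, 20% dropout, null rate 15%, target rate 40%, success at ten or more. The 32 and the 20% recur in the executive summary. The requirement of two cycles for evaluability is from Efficacy evaluation.

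**1. Reproducing the stated figure.** The article prints no formula. Adding 20% to the required number gives 27 x 1.2 = 32.4, which rounds to 32. The stated target is consistent with that calculation, but that it was the one used is an inference.

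**2. What 32 recruits deliver.** 32 x (1 - 0.20) = 25.6, so 25 to 26 evaluable patients are expected.

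**3. What 27 evaluable patients need.** 27/(1 - 0.20) = 33.75, rounded up to 34. Check: 34 x 0.8 = 27.2.

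**4. The loss that 32 can absorb.** 32 - 27 = 5 patients, and 5/32 = 15.6%.

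**5. Chance of reaching 27.** Assume that each recruit is evaluable independently with probability 0.8, so the number evaluable is binomial:

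- 32 recruited: P(at least 27) = 0.36
- 34 recruited: P(at least 27) = 0.63

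**6. Power of a rule on evaluable patients, stated cut-off of ten, true rate 40%.** The power for a fixed number evaluable is P(Bin(n, 0.40) >= 10):

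| Evaluable | Power |
|---|---|
| 27 | 69.1% |
| 26 | 63.6% |
| 25 | 57.5% |

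Averaged over the binomial number evaluable in step 5:

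| Recruited | Average power |
|---|---|
| 32 | 60.2% |
| 34 | 68.8% |

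The comparison that belongs to this point is 60% against 69%, about 9 percentage points. The distance from 69% to the stated 90% exists even with all 27 patients evaluable. It comes from the pairing of a cut-off of ten with 27 patients, which is a separate matter.

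**The case against.** Four arguments can be made on the other side.

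*It is two patients.* True: 34 against 32. The slip is small, and the wording could loosely mean an allowance of 20% added to 27. That reading explains where 32 came from, but it does not produce 27 evaluable patients when 20% of recruits are lost. In an exact design of this size, one evaluable patient moves power by 5 to 6 points at the stated cut-off (69.1%, 63.6%, 57.5%).

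*The primary analysis does not use the evaluable set.* This stands and limits the consequence. Patients who were dosed but did not complete two cycles remain in the intention-to-treat set, so 25.6 evaluable patients does not mean 25.6 in the primary analysis. For illustration, if all 32 were dosed and assessed at 6 months, and the 40% rate applied to all of them, ten or more of 32 would have an upper-tail error of 0.0156 at a rate of 15% and power of 88.4%. The sample-size paragraph nevertheless states its requirement and its rule for evaluable patients, so the sentence on recruitment remains wrong.

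*The power loss is mostly not due to dropout.* A reader might see 60% beside the stated 90% and charge the whole gap to the inflation step. The figures do not support that, because power is already 69.1% with the full 27. Nor should the loss be described with a lower cut-off such as eight. The article states no such cut-off, and with 25 or 26 evaluable patients it would have upper-tail errors of 0.0255 and 0.0321, above the 0.025 implied by the stated two-sided 0.05.

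*Restating the allowance fits the assumption to the sample size.* This is fair as a caution. The article gives no evidence for 15% any more than for 20%. The restated figure should therefore be presented as the loss that 32 can tolerate, not as a new forecast.

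**Conclusion.** The point holds as an arithmetic inconsistency of modest size. The figures 27, 32 and 20% cannot all be right: 32 recruits with a 20% loss give 25.6 evaluable patients, 34 would be needed, and 32 covers a loss of 5 (15.6%). These results need only the article's own numbers.

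The probabilities of 36% and 63%, and the average powers of about 60% and 69%, rest on three further assumptions: independent loss at exactly 20%, a 40% rate among evaluable patients whoever is lost, and a decision rule of ten or more applied to evaluable patients.

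A reader might infer that the primary analysis is underpowered because of the inflation step. The document does not support that, since the primary analysis set is all dosed patients. It also does not establish how 32 was obtained; multiplication by 1.2 fits but is not stated.

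**What to change.** Keep 32 and correct the allowance in both places, Planned sample size and the executive summary, to say that up to 5 of the 32 patients (about 15%) may be non-evaluable. If the sponsor still expects 20%, say instead that 25 to 26 evaluable patients are expected, and give the power of the trial's own decision rule at that number.

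If the base design (27 patients, cut-off of ten) is itself corrected, the recruitment target must be recalculated from the new number as n/(1 - dropout), and 32 should not be carried over.

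The cost is one corrected figure in two places and no extra patients. The stated tolerance, or the stated power, becomes somewhat less favourable.
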